## Discussion

3

This study provides a protocol for cross‐cultural adaptation and psychometric assessment of the FACIT‐Pal scale in the Persian‐speaking population. The FACIT‐Pal scale is being used to measure the quality‐of‐life and palliative care intervention outcomes in several languages, such as Spanish [37], German [38], Turkish [36], African languages [29], and recently in Chinese [39].

Bagcivan et al. have translated FACIT‐Pal into Turkish and assessed its psychometric properties [36]. Their research has shown that the FACIT‐Pal‐TR owns strong psychometric validity and reliability. The Cronbach's alpha coefficient in the Turkish version was 0.932 and also test–retest scores had shown a significant relationship (*r* = 0.877, *p* < 0.001). As the Iranian and Turkish people have a lot in common in terms of religion, history, and culture [49], it is anticipated that the Persian version of FACIT‐Pal will have the same strength in terms of psychometric properties.

Additional research demonstrating the potential for the FACIT‐Pal questionnaire has been conducted by [name] et al.'s team who translated and psychometrically validated the FACIT‐Pal‐14—the shortened version of 46‐item FACIT‐Pal—in Persian to measure the patient's quality‐of‐life within a randomized controlled trial. Despite the focus of most articles on measuring the quality‐of‐life in cancer patients, in this article, patients with heart failure have also been included [50]. This is a promising potential for the Persian version of the 46‐item FACIT‐Pal to be an applicable scale for measuring QoL. In Iran, palliative care is mainly focused on cancer and specifically on the physical aspect of the patients; whereas this research shows the feasibility of the FACIT‐Pal‐14 validation among Iranian people suffering from heart failure [51].

In the Iranian context, there are alternative FACIT scales with different subscales. Out of these, the Persian version of FACIT‐Sp has been validated in 2013 by Jafari et al. the goal of their study was to translate and investigate the reliability and validity of the Persian version of the FACIT‐Sp among Muslim Iranians in treatment for cancer. The Cronbach's alpha coefficient in the Persian version of FACIT‐Sp ranged from 0.72 to 0.90, which showed sufficient reliability [52]. Similar to this study, our research will be conducted among Iranian patients who are predominantly Muslim. However, the focus of this study was limited to patients diagnosed with cancer.

The concept of palliative care is not sufficiently understood by the public and also health‐care staff, which has led to a lack of knowledge about its beneficial outcomes [50]. A reliable and valid tool for measuring quality of life is essential for evaluating the quality of services, the effectiveness of care and treatments, and the impact of interventions [53]. Also, it is mentioned that the community and cultural context could significantly impact the feasibility of the interventions that are implemented, and this shows how culture could be tremendously effective [40]. Moreover, the lack of a gold standard questionnaire, along with a variety of quality‐of‐life scales, has made it difficult to make a comprehensive evaluation of quality‐of‐life [53]. The FACIT‐Pal instrument has yet to be translated into Persian and assessed psychometrically in Iranian culture. Thus, this study could be an outstanding step approaching the optimum quality‐of‐life in Iranian people receiving palliative care.

### Limitations

3.1

Using a self‐report data collection method may introduce potential response bias. To minimize this risk, the researcher will provide clarification for any ambiguous questionnaire items to ensure that participants fully understand the content. Nevertheless, the possibility of social desirability bias and recall bias cannot be completely ruled out. Another limitation concerns the generalizability of the findings. This study uses a single‐center sample recruited exclusively from the Imam Khomeini Hospital Complex, a major tertiary referral center. Although patients with cancer and heart failure—two of the most common chronic disease groups—were selected to enhance generalizability, the results may not be representative of patients in rural, non‐academic, or community‐based settings. Future multi‐center validation studies are recommended. Furthermore, the cross‐sectional design of this study does not allow for assessment of test–retest reliability, and therefore temporal stability of the Persian FACIT‐Pal remains unknown. In addition, although the cognitive interview sample of 10 participants follows FACIT translation and linguistic validation guidelines, it may not fully capture Iran's linguistic, cultural, and dialectical diversity. This limited sample size may affect the comprehensiveness of cognitive debriefing, and future studies with larger and more diverse samples are warranted.

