### Phase 1: Cross‐Cultural Adaptation and Harmonization

2.2

The copyright of the FACIT questionnaires entirely belongs to the FACIT organization. This study will be conducted after obtaining the written permission letter from the FACIT organization, using the standardized multilingual and validation measurement system [44, 45]. This ensures that the translation of the FACIT‐Pal questionnaire into Persian contains the sufficient quantitative criteria equivalent to the original version of FACIT‐Pal [46]. The written permission was obtained from FACIT.org on September 2, 2024.

The translation phase consists of two forward translations, one reconciliation of the two forward translations, and one backward translation. Initially, two bilingual Iranians—literate in English—will translate the English version to Persian (Forward translation). Afterward, another Persian‐speaking person makes a unified version of the Persian version out of the two forward translations. This unified version is then translated into English by an English‐speaking bilingual who is literate in Persian. If no translation issues are identified, an expert in the field of medical sciences will review the final version of the Persian translation and, if there are any content problems, will express his/her opinions to the team leader.

Once the Persian translation is finalized, cognitive structured interviews will be conducted based on the organization's standard guidelines. This will involve one experienced researcher who is familiar with the questionnaire, palliative care, and qualitative studies, and who has cognitive interview experience. Ten Persian‐speaking patients will complete the FACIT measure and their feedback will be analyzed to further refine the translation, if necessary. After the final application of the patients’ comments, the process of translation and harmonization of the questionnaire will be completed. It is noteworthy that all these steps will be supervised by [name], the Translations Manager of the FACIT organization, and the principal investigator of the research team, [name], will remain in contact with him throughout the translation process.

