##### Participants

2.3.1.1

The study sample will be divided into two groups: (1) Patients with heart failure, comprising 50 percent (276 patients) of the total sample size, will be recruited from CCU, cardiology wards, and the heart failure clinic of IKHC; and (2) Patients with cancer: comprising 50 percent (276 patients) of the total sample size, will be recruited from the cancer institute (oncology ward) of IKHC and the cancer clinics of IKHC. The inclusion criteria will be: (1) consent to participate in the study; (2) diagnosed with heart failure or cancer; (3) 18 years of age or older; (4) having the literacy to read and write in Persian. The exclusion criteria will be: (1) presence of a documented, untreated severe psychological disorder recorded in the medical record by a psychiatrist or treating physician, including schizophrenia spectrum disorders, bipolar disorder, or active substance use disorder, which is considered to cause significant functional impairment, defined as impaired judgment, cognition, or communication that interferes with the individual's capacity to understand study procedures or complete study assessments; (2) uncorrected communication impairments (auditory, visual, or verbal) that preclude participation; and (3) completion of less than 80% of the study measures.

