### Sampling Process

2.5

Among the individuals with cancer and heart failure referred to the inpatient wards and heart failure and cancer outpatient clinics of the IKHC, 552 patients will be selected as the research sample by the convenience sampling method, based on inclusion and exclusion criteria. Of the desired sample size, 50% will be allocated to patients with heart failure (276 patients) and 50% to patients with cancer (276 patients). The necessary matters regarding the study process, the objectives of the research, as well as the confidentiality of their information, will be explained to the patients, and they will be invited to participate in the present study if they wish. Written informed consent will be obtained, and the research instruments, including the demographic questionnaire and the FACIT‐Pal questionnaire, translated into Persian, will be provided. Patients will be asked to complete the questionnaire using a self‐report approach.

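### Letting the researcher clarify ambiguous items in the Phase 2 survey mixes aided with unaided answers and may mask wording faults that the ten interviews missed

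*Protocol article*

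**What the plan says.** Under Study Design and Setting (2.1), the aim is to assess the psychometric properties of the Persian version. Sampling Process (2.5) sets the mode: "Patients will be asked to complete the questionnaire using a self‐report approach". Participants (2.3.1.1) supports that mode with an inclusion criterion: "having the literacy to read and write in Persian".

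Wording problems belong to Phase 1 (2.2). After the translation steps, "Ten Persian‐speaking patients will complete the FACIT measure and their feedback will be analyzed to further refine the translation, if necessary". Once those comments are applied, "the process of translation and harmonization of the questionnaire will be completed".

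Limitations (3.1) begins: "Using a self‐report data collection method may introduce potential response bias". As the remedy it states that "the researcher will provide clarification for any ambiguous questionnaire items to ensure that participants fully understand the content". It then concedes that social desirability and recall bias may remain and, of the ten interviews, that "This limited sample size may affect the comprehensiveness of cognitive debriefing".

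**The concern.** A validation survey tests whether the fixed text works when patients read and answer it. If a researcher explains an item, the patient answers the item plus the explanation, and the explanation may differ from one patient to the next. An item that needs explaining is evidence about the translation. Resolving it patient by patient removes that evidence from the responses.

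Three results are exposed:

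- **Reliability and CFA.** Alpha, omega, loadings and fit would describe a blend of aided and unaided completion.
- **Invariance between cancer and heart failure.** The two groups are recruited from different wards and clinics. If help is more frequent in one group, it is confounded with disease in the multiple-group comparison.
- **Detection of residual wording faults.** The plan itself says that ten interviews may be incomplete. Phase 2 is the next stage at which missed faults could show, and clarification tends to cover them.

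The stated reason is also weak. Clarification can reduce misunderstanding, which is one source of response error. It does not reduce social desirability or recall bias, and a researcher's involvement could add to the former.

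**Working it through.** **Setting the sections side by side.** Section 2.2 closes the wording after Phase 1. Section 2.5 has that wording completed by self-report. Section 3.1 has the researcher explain any item found ambiguous during that completion. No other section limits this to neutral help such as re-reading. The clarification is a stated procedure, not a gap.

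**Can the size be computed?** No. The article gives no rate of ambiguous items and no rate of help. What follows shows only how sensitive alpha could be, under assumptions.

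Inputs from the article:

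- the palliative section has k = 19 items, with an English alpha of 0.82 (2.4);
- the benchmark for adequate reliability is 0.7 (2.6.1).

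Assumptions, none of them from the article:

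- one factor with equal loadings for sound items;
- m faulty items that load 0 or 0.2 unaided;
- a share c of patients given clarification;
- clarification that fully restores a faulty item.

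*Step 1, calibrate.* Mean inter-item correlation r = α / (k − (k − 1)α) = 0.82 / (19 − 18 × 0.82) = 0.82 / 4.24 = 0.193. The loading is √0.193 = 0.44. Check: 19 × 0.1934 / (1 + 18 × 0.1934) = 3.675 / 4.481 = 0.82, the article's figure.

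*Step 2, formula.* α = k/(k − 1) × (1 − k/S), where S is the sum of all entries of the inter-item correlation matrix. A faulty item with unaided loading λ₀ is given the loading λ₀ + (0.44 − λ₀) × c.

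*Step 3, example.* Take six items loading 0 with no help. S = 19 + 13 × 12 × 0.1934 = 49.17, so α = (19/18) × (1 − 19/49.17) = 0.648.

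*Step 4, range of alpha.*

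| Faulty items (unaided loading) | c = 0 | c = 25% | c = 50% | c = 100% |
|---|---|---|---|---|
| 1 (0) | 0.799 | 0.805 | 0.810 | 0.820 |
| 3 (0) | 0.749 | 0.770 | 0.788 | 0.820 |
| 6 (0) | 0.648 | 0.704 | 0.750 | 0.820 |
| 1 (0.2) | 0.809 | 0.812 | 0.815 | 0.820 |
| 3 (0.2) | 0.785 | 0.794 | 0.803 | 0.820 |
| 6 (0.2) | 0.743 | 0.765 | 0.785 | 0.820 |

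Only six of 19 items loading zero takes alpha below 0.7 unaided. In that case help to a quarter of patients lifts it just over the benchmark. With one faulty item the change is about 0.02 at most.

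*Step 5, direction.* The table rises from left to right because clarification was assumed to restore the item. It does not prove the direction. If inconsistent explanations instead pulled three sound items down from 0.44 to 0.2, alpha would fall from 0.820 to 0.785.

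**The case against.** The strongest reply is that the effect is limited and speculative. Patients must be literate in Persian and fill in the form themselves. Help is foreseen only for ambiguous items. Such items would have to survive two forward translations, reconciliation, back-translation, expert review, supervision by the scale's owner and the interviews. The Phase 2 outputs in 2.6.1 do not include item comprehensibility. Correcting a misunderstanding also removes some response error. Most of this stands, and it limits the severity. It does not justify unscripted explanation in a survey whose purpose is to test the text.

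A reader might infer more than the article supports:

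- *That the data as a whole no longer test the Persian wording.* Only clarified answers are affected. All 46 items and all 552 patients are a ceiling, and nothing suggests routine assistance.
- *That the results must be too favourable.* Repair of faulty items would flatter them, but variable explanations would add noise. Optimism is likely, not certain.
- *That help will go unrecorded.* The article is silent on this. A condensed article commonly leaves forms and staff instructions to the full protocol, so the silence is no finding.
- *That one disease group will receive more help.* This is possible given the separate recruitment sites, but nothing in the text says so.

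**Conclusion.** The point holds at moderate severity. The planned clarification conflicts with assessing a finished translation by self-report. For the items and patients concerned, the psychometric results will rest on wording plus explanation, and residual translation faults may be masked. The reason given covers misunderstanding at best, not the two biases that the section leaves open.

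The size cannot be derived from the article. Under the assumptions shown, it runs from negligible (one faulty item) to enough to cross the 0.7 benchmark (six items of no value unaided). The latter is an extreme case, and both rest on inputs that the article does not give. The reason to act before data collection is that aided answers cannot be separated afterwards unless they have been recorded at the time.

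**What to change.** Replace the sentence in Limitations, and place the rule with the administration procedure in 2.5:

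> *Staff will not explain or rephrase item content; they may re-read the item verbatim and ask the patient to answer as he or she understands it; each request for help is recorded by item and patient.*

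Then:

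- report the request rate per item;
- keep all patients in the main analysis;
- repeat reliability and CFA without the questionnaires where help was requested, as a sensitivity analysis only, because dropping them selects patients who found the items easy;
- no longer present clarification as a remedy for response bias.

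The cost is one sentence and a tally on the case form. The downside is slightly more item non-response, which may move a few patients below the 80% completion rule. If that rule is applied to the 46 FACIT-Pal items alone (an assumption), 0.80 × 46 = 36.8, so a patient is excluded only with ten or more blanks (36/46 = 78%; nine blanks leave 37/46 = 80.4%). Report the number excluded by disease group.

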## Ethics Statement

The study protocol was approved by the Institutional Review Board at Tehran University of Medical Sciences (Code: IR. TUMS. MEDICINE. REC.1403.432). All participants will provide written informed consent.

## Consent for Publication

The authors have nothing to report.

## Data Availability

No datasets were generated or analyzed during the current study.
